**Discussion:**

This pragmatic clinical trial approach will integrate a predictive machine-learning algorithm into a workflow process and evaluate the effectiveness of the intervention. We will compare the use of in-person interpreters and time to first interpreter use between the control and intervention groups.

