### Aims of the study

The aim of this study is to assess the effectiveness of our comprehensive intervention, integrating artificial intelligence (AI) with a human operator into the language services process to provide in-person interpreters to patients with complex care needs. The study will focus on evaluating the impact of the combined human-AI intervention, along with the defined process (active outreach to healthcare teams caring for identified patients) on in-person interpreter utilization in the target population. *Hypothesis statement*: By employing a machine learning algorithm to identify individuals with NELP and complex care needs, patients will be more likely to receive an in-person interpreter and at an earlier stage of the hospitalization compared to standard care.

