### Trial design

To achieve the objectives, we will conduct a two-armed stepped wedge cluster randomized trial in both inpatient campuses at Mayo Clinic, Rochester. Trial units will undergo a HIT assessment of patients who would benefit from in-person interpreter support, allowing a human operator (CTO) to validate the forecast and notify the language services about the identified patient needs. Patients in control units will receive usual standard of care relying on their clinicians to reach out to interpreter services to request an in-person interpreter or use another type of interpretation modality such as video or phone.

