### Outcomes

For all study outcomes, data will be collected through either the EHR or language services report list. The data outcomes will be abstracted during the patient hospitalization. The primary outcome is the number of patients with NELP and complex care needs who use an in-person interpreter during hospitalization in the units of interest as measured by language services daily report list. The secondary outcome will be time to first use of in-person interpreter—measured as time in hours and minutes from admission to in-person interpreter use as measured by the language services team electronic documentation system. The secure chat process measures including if sent, if responded to, and if not sent the reason such as no in-person interpreter on staff or available that day will be collected daily.

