### Data analysis plan

#### Power statement

The proposed investigation will use a stepped wedge cluster randomized design with 12 clusters. Based on preliminary data, it is estimated that there are > 9000 inpatient admissions with NELP annually at our institution of which only 14 to 16% use the services of an in-person interpreter at some point during their hospitalization. For sample-size/statistical power considerations, we assume that the proportion of patients with NELP receiving in-person interpreter services at the start of our study period (while all patients are receiving usual care) will be 0.15. Although not all inpatients with NELP will meet study inclusion criteria, we believe that over the course of the year, the total number of inpatients who meet study inclusion criteria will be in the range of 500 to 700 for each of the 12 clusters. Stepped wedge cluster randomization trials typically have more statistical power than other cluster randomized designs when clusters are correlated, because each cluster is able to serve as its own control. Within-cluster correlation was introduced by using cluster-specific baseline rates (which ranged between 10 and 20%), and within-cluster correlation coefficients were not specified. Because of the complex nature of the design, we estimated statistical power using Monte Carlo simulation [70]. The Monte Carlo simulation for this paper was generated using the SAS software (Copyright © [2024] SAS Institute Inc. SAS and all other SAS Institute Inc. product or service names are registered trademarks or trademarks of SAS Institute Inc., Cary, NC, USA.) A logistic regression model was used for the simulation with the outcome being the use of in-person interpreter services. Simulations were created with the overall baseline percentage of patients receiving in-person interpreter services set at 15% (with cluster-specific baseline rates set between 10 and 20%) and included slight upward secular trend over time. Supplemental Table S2 presents the statistical power provided for detecting potential intervention effects corresponding to odds ratios ranging from 1.35 to 1.65 using 3 various sample size scenarios (500, 600, and 700 patients per cluster). Based on these simulations, the proposed investigation should have statistical power of > 80% to detect an odds ratio of 1.5 or greater.

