We will generate overall and cluster-specific summaries of patient characteristics (sex, age, primary language, risk scores, etc.) using descriptive statistics, including mean ± SD for continuous variables with frequencies and percentages for nominal variables. The entire study population will be analyzed following an intention-to-treat (ITT) approach. The ITT analysis will include all patients in the intervention group regardless of whether the secure chat was sent and regardless of whether the clinician requested the service after receiving the secure chat. This principle will be extended to the cluster status in the event of transfers between intervention and control units. All missing data will be analyzed using complete case analysis. The primary outcome will be a binary variable representing any use of interpreter services during hospitalization. To assess the effects of the intervention, the primary outcome will be analyzed using a generalized linear mixed-effects model with variables: intervention approach and time period. The inpatient unit will be denoted as the random effect in the model to characterize the correlation among patients within the same cluster. An additional secondary outcome will be evaluated as the time from “intervention” to first use of an interpreter. Eligible patients are identified at 7 am daily, Monday to Friday. Time of intervention is calculated from the first time a patient is identified until documentation of first use of an interpreter. Patients may be eligible on multiple days and calculation of this outcome will start evaluation at 7 am on the first eligible day identified by the CTO. Those who never receive an interpreter will be assigned an adverse value (an arbitrarily large amount of time, reflecting an outcome worse than any observed time to interpreter). A generalized linear mixed-effects model with proportional odds link function will be used to evaluate this outcome to account for the stepped wedge cluster randomized study design including adjustment for time period and random effect for cluster. An alternative approach may consider reporting cumulative incidence estimates of time to interpreter by intervention group, with death or discharge a competing risk, which is functionally similar to the assignment of large arbitrary value for those without interpreter services. Patients who received interpreter services prior to identification by the CTO will be excluded from analyses as they do not meet inclusion criteria at “time zero” or baseline of the analysis. In all cases, the intervention effect will be summarized by reporting point estimates and corresponding 95% confidence intervals. Two-tailed *p*-values < 0.05 will be considered statistically significant [71, 72].

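### The analysis paragraph drops 'in-person' from the primary outcome, the secondary outcome and the prior-use exclusion, contradicting the in-person endpoint stated elsewhere in the protocol

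*Protocol article*

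**What the plan says.** The protocol article names the primary endpoint in several places.

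- **Outcomes:** "The primary outcome is the number of patients with NELP and complex care needs who use an in-person interpreter during hospitalization".
- **Aims of the study (hypothesis):** "patients will be more likely to receive an in-person interpreter and at an earlier stage of the hospitalization compared to standard care".
- **Abstract, Discussion:** "We will compare the use of in-person interpreters and time to first interpreter use between the control and intervention groups".
- **Power statement:** "A logistic regression model was used for the simulation with the outcome being the use of in-person interpreter services", and "Simulations were created with the overall baseline percentage of patients receiving in-person interpreter services set at 15" per cent.
- **Analysis paragraph, directly after the power statement:** "The primary outcome will be a binary variable representing any use of interpreter services during hospitalization".

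The analysis paragraph is the only text that specifies the variable entering the primary mixed-effects model, and the term 'in-person' does not occur in it. Its secondary outcome runs to first use of an unspecified interpreter, whereas the Outcomes section times first in-person use. Its exclusion for prior use also refers to interpreter services without a modality.

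The protocol does separate the modalities. Under Trial design, clinicians in control units may "request an in-person interpreter or use another type of interpretation modality such as video or phone". The Intervention section draws the same distinction for control patients.

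**The concern.** As written, the plan contains two primary endpoints: in-person use, and use of any interpreter service. The second is broader, because phone and video belong to usual care. Applied literally, the analysis paragraph has three effects.

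1. A control patient with one video call counts as a success.
2. A patient whom the intervention moves from video to in-person counts as a success either way, so the change the trial seeks leaves no trace.
3. Anyone who had a phone or video interpreter before being identified by the Control Tower Operator, for example in the emergency department, leaves the analysis. That alters the population as well as the endpoint.

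The base rate and the power were set for in-person use and have no stated counterpart for any use. Two analysts could build different primary variables from the same text. The Participant timeline section says the analysis will not be blinded, so the choice should not remain open.

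**Working it through.** **Step 1. Reproduce the stated power for the in-person endpoint.** Inputs from the Power statement: 12 clusters of 500, 600 or 700 patients, baseline 15% with cluster rates of 10% to 20%, a slight upward trend, OR 1.5. Two-sided alpha is 0.05 (analysis paragraph), with 5 steps (Participant timeline). Assumed: a trend of 0.02 on the log-odds scale per period. Method: a logistic model with cluster and categorical period effects, with power from the expected information and a 400-run Monte Carlo check.

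| Patients per cluster | Expected information | Monte Carlo |
|---|---|---|
| 500 | 92% | 89% |
| 600 | 96% | 96% |
| 700 | 98% | 98% |

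Variants with 3, 4 or 6 steps, or 35 clusters at the same total, also lie between about 89% and 98%. The protocol's claim of more than 80% is therefore consistent with its inputs for in-person use. Supplemental Table S2 is not shown, so only this bound could be checked.

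**Step 2. Convert the effect to a risk difference.** Baseline odds are 0.15/0.85 = 0.1765. Multiplying by 1.5 gives 0.2647, and 0.2647/1.2647 = 0.209. In-person use rises from 15% to 20.9%, which is 5.93 percentage points.

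**Step 3. Translate to any use.** Let p be the control any-modality rate and f the share of added in-person users who would otherwise have had phone or video. Any use rises by d = 0.0593 × (1 − f). The documents give neither p nor f.

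**Step 4. Proportional draw.** Added in-person users can come only from the 85% not already using one. If they are drawn from these at random, f = (p − 0.15)/0.85, so 1 − f = (1 − p)/0.85 and d = 0.0593 × (1 − p)/0.85.

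| Assumed p | d | Any use under intervention | OR |
|---|---|---|---|
| 30% | 0.0488 | 0.3488 | 1.25 |
| 50% | 0.0349 | 0.5349 | 1.15 |
| 80% | 0.0140 | 0.8140 | 1.09 |
| 90% | 0.0070 | 0.9070 | 1.08 |

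Example at 50%: 0.5349/0.4651 = 1.15, divided by baseline odds of 1. With 12 clusters of 600 and any-use cluster rates spread 5 points either side of p, power under this draw is 69% at p = 30%, 38% at 50%, 20% at 70% and 11% at 85%. A second calculation (35 units, 6 periods, 6,000 patients, between-unit SD 0.231 on the log-odds scale) gives 97% for the in-person endpoint, and 38%, 14% and 9% for any use at 50%, 80% and 90%.

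**Step 5. Wider substitution shares** (12 clusters of 600, p from 30% to 85%):

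| f | d | OR | Power |
|---|---|---|---|
| 0 | 0.0593 | 1.27 to 1.77 | 80% to 99% |
| 0.5 | 0.0297 | 1.13 to 1.29 | 29% to 55% |
| 0.75 | 0.0148 | 1.06 to 1.13 | 10% to 18% |
| 1 | 0 | 1 | 5% |

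**The case against.** The best reply is that the authors meant in-person throughout.

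- The abstract drops the modifier for time to first use, which the Outcomes section defines as in-person.
- The intention-to-treat sentence speaks of the service requested after the secure chat, and that chat offers only in-person interpreters.
- 'Any use' can simply mean at least once, the patient-level form of the count in Outcomes.
- The Outcomes section names the language services daily report as its source, and no section plans to record phone or video use as an outcome.

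This makes shorthand plausible, perhaps likely. It does not remove the contradiction. Nothing in the analysis paragraph says the term is restricted, the power paragraph just before it writes 'in-person' repeatedly, and Data management draws outcomes from the EHR as well as the language services report. Nor is this a detail left to an analysis plan, because the article states a definition that conflicts with its own outcome.

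A reader might infer that the trial will fail to test its hypothesis, or that its effect will largely cancel. The documents do not support that. It would need an analyst to follow the literal wording over the Outcomes section, and also a high substitution share, which is not given. If most new in-person users would otherwise have had no interpreter, little cancels. A reader might also see a conflict between a number of patients and a binary variable; there is none, since one is the sum of the other. The difference between 12 clusters and 35 units is a separate matter and hardly changes these figures.

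**Conclusion.** The contradiction stands and concerns the primary endpoint. The analysis paragraph is broader than the outcome, hypothesis, abstract and power simulation. Taken at its word, it changes the endpoint and, through the prior-use exclusion, the analysis population. For that endpoint the 15% base rate and the stated power have no basis; for the in-person endpoint the stated power reproduces.

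The size of the loss is conditional. The dilution of an OR of 1.5 to between 1.25 and 1.08 rests on assumed any-use rates of 30% to 90% and a proportional draw. The power range of about 5% to 99% reflects substitution from complete to none. These figures show why the wording matters and do not predict the trial's result. The point should be settled before analysis because it decides which variable is tested.

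**What to change.** In the analysis paragraph, define the primary variable as any in-person interpreter use during hospitalization (yes/no). Insert 'in-person' in the secondary outcome and in the prior-use exclusion, so that all three agree with the endpoint in the Outcomes section. If the analysis plan repeats the unqualified wording, correct it in the same way.

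The contradiction requires no more than this. Restricting the primary variable to use after identification, or adding any-modality use as a further outcome, would be separate decisions.

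The cost is wording only. The Outcomes section already takes in-person use from the language services daily report, and neither the design nor the sample size changes.

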### Participant timeline

The stepped wedge design involves allocating 35 floor and ICU units into a design matrix comprising 5 treatment wedges. Computer allocation will be used to generate the allocations prior to the start of the study. Each unit will cross over randomly from the control group (standard clinical practice and care) to the intervention group. Each wedge will span approximately 60 days, resulting in a study period of approximately 12 months unless specified otherwise. The initial step will entail a baseline period during which no intervention is administered, with all clusters receiving the intervention in the final step. Due to the pragmatic design of the trial, clinicians cannot be blinded to patient allocation to the intervention or control units, and we do not plan to implement blinding during the analysis as our endpoints are objective, and diffused roll-out would make this impossible [69]. This is most relevant if there are patient-reported outcomes. Patients will receive standard in-person interpreter services if requested and available in the hospital; however, those in the intervention group will differ in that clinicians will have been alerted to the patient’s need based on complexity score, CTO review and filter and secure chat sent by language services personnel. No additional patient data beyond the hospitalization will be collected, and there will be no follow-up visits. See Fig. 2.

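### The optional cumulative-incidence comparison by arm omits period and unit; read as an effect estimate, it would absorb any secular trend

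*Protocol article*

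**What the plan says.** All of the analysis text stands in the Protocol article, Data analysis plan, in the paragraph that follows the power calculation.

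- **Main secondary analysis.** Time to first interpreter use is analysed with a proportional-odds mixed model, chosen "to account for the stepped wedge cluster randomized study design including adjustment for time period and random effect for cluster".
- **Alternative.** The next sentence reads: "An alternative approach may consider reporting cumulative incidence estimates of time to interpreter by intervention group, with death or discharge a competing risk". It names neither period nor unit. Its closing clause describes the option as one "which is functionally similar to the assignment of large arbitrary value for those without interpreter services".
- **Inference.** Later in the same paragraph: "In all cases, the intervention effect will be summarized by reporting point estimates and corresponding 95% confidence intervals". The significance rule is two-sided, and by it p-"values < 0.05 will be considered statistically significant".
- **Design.** Under Participant timeline: "The initial step will entail a baseline period during which no intervention is administered, with all clusters receiving the intervention in the final step".
- **Trend.** The power simulation "included slight upward secular trend over time". No size is given.

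**The concern.** In a stepped wedge, control patients come mostly from early calendar time and intervention patients mostly from late calendar time. Two curves defined only by arm differ if the intervention works, but also if in-person interpreter use drifts over the year for any other reason. The main model separates the two explanations with its period terms. The alternative, followed as written, does not.

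If the by-arm contrast were reported as an effect, an upward drift would look like earlier and more frequent interpreter use under the intervention. A true harm could be masked in the same way, and a downward drift would bias against the intervention. Because units differ in baseline use, an interval that ignores unit is also too narrow when there is no drift at all.

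**Working it through.** **1. Inputs.** From the documents: 35 units in 5 wedges, 7 units per wedge, 60-day steps, a first period all in control and a last period all in intervention (Participant timeline; Intervention). From the Power statement: overall baseline 15%, "with cluster-specific baseline rates set between 10 and 20" percent; 12 clusters of 500 to 700 patients; more than 80% power at an odds ratio (OR) of 1.5. Assumed here: six equal periods, equal enrolment per unit-period, and a common trend OR per period of 1.00 to 1.05.

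**2. The plan's own figure.** Simulated cluster-period counts were analysed by logistic regression with intervention, period and cluster (fixed cluster effects standing in for the random effect). With 12 clusters, OR 1.5 and trend 1.02, power is 94% for 500 patients per cluster, 96 to 97% for 600 and 97 to 98% for 700. This agrees with the stated figure of more than 80%.

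**3. How far arm and period overlap.** Number the periods j = 0 to 5. Period j has 7j intervention units and 7(5 − j) control units.

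- Control mean period: Σ j(5 − j) / Σ (5 − j) = 20/15 = 1.33.
- Intervention mean period: Σ j² / Σ j = 55/15 = 3.67.
- Gap: 35/15 = 2.33 periods; × 60 = 140 days.
- Each arm has 105 unit-periods, so the covariance of arm and period is 2.333 × 0.25 = 0.583. The SD of period is √(35/12) = 1.708 and the SD of arm is 0.5. Correlation = 0.583 / (1.708 × 0.5) = 0.68.

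The confounding is strong but partial: the four middle periods contain both arms.

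**4. Spurious effect from trend alone.** With no intervention effect, the crude log OR is about 2.33 × ln(trend OR).

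- Trend 1.02 (15.0% rising to 16.3%): exp(2.333 × 0.0198) = 1.05.
- Trend 1.05 (15.0% rising to 18.4%): exp(2.333 × 0.0488) = 1.12. By arm this is 15.9% against 17.4%.

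**5. Simulation with true OR 1.** The crude comparison uses arm only, on end-of-stay incidence; the adjusted one adds period and unit. There are 12 clusters of 600 (2,000 replicates) or 35 units sharing about 7,200 patients (600 replicates). Tests are two-sided at 5%.

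| Trend OR per period | Layout | Crude OR | Crude rejects | Adjusted OR | Adjusted rejects |
|---|---|---|---|---|---|
| 1.00 | 12 clusters | 1.00 | 18.4% | 1.00 | 5.0% |
| 1.00 | 35 units | 1.01 | 8.7% | 1.01 | 3.5% |
| 1.02 | 12 clusters | 1.05 | 22.8% | 1.00 | 5.1% |
| 1.02 | 35 units | 1.05 | 15.7% | 1.00 | 4.0% |
| 1.03 | 12 clusters | 1.07 | 31.2% | 1.00 | 4.7% |
| 1.03 | 35 units | 1.07 | 20.3% | 1.00 | 6.0% |
| 1.05 | 12 clusters | 1.12 | 46.8% | 1.00 | 5.5% |
| 1.05 | 35 units | 1.12 | 45.7% | 1.00 | 5.5% |

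Monte Carlo error, √(p(1 − p)/R), is about 1 to 2 points for the crude rejection rates under a trend. At trend 1.05 nearly all rejections favour the intervention (46.3 of 46.8 points; 45.5 of 45.7). A separate simulation of 35 units and 7,200 patients, with unit baselines drawn uniformly from 10 to 20%, gave 14% and 44% at trends 1.02 and 1.05; a Gray-type test on the curves agreed within 1 point. The rows with no trend show the cost of ignoring unit alone.

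**6. Masked harm.** With a true OR of 0.90 and trend 1.05, the crude OR is about 0.90 × 1.12 = 1.01. The adjusted model returned 0.91.

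**The case against.** The case against is that silence is being read as specification. The sentence is permissive, concerns a secondary outcome, and names no test. Saying by intervention group states the contrast without ruling out adjustment, and an article may leave model terms to a full protocol or SAP that is not shown. The authors plainly know the issue, since both specified models carry period and unit. The sentence on reporting effects in all cases could be meant for those models only.

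Much of this stands, and it limits the point. Several stronger readings are tempting but not supported:

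- That the alternative simply tests early against late calendar time. It does not; the middle periods hold both arms.
- That the protocol predicts a rise in use. It only put a slight trend into a power simulation. A trend of 1.10 per period (15% to 22.1%) produces far larger rejection rates but is hard to call slight, so it is not relied on here.
- That calling the approaches functionally similar is an error. The comparator in that clause is the value assigned to patients without an interpreter, and for that purpose the statement is fair.
- That the trial's main conclusions are at risk. Nothing says the alternative replaces the main model.

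What does not fall away is the contrast between adjacent sentences. The design adjustment is spelled out for one method and absent from the other, nothing marks the curves as descriptive, and the paragraph's general rule asks for an effect estimate with an interval.

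**Conclusion.** The point holds as a limited one. The optional by-arm cumulative-incidence comparison, if followed as written and read as an effect estimate, is partly confounded with calendar period and ignores unit clustering. With no true effect and an assumed trend OR of 1.02 to 1.05 per period, the crude OR is about 1.05 to 1.12 and a nominal 5% test rejects in roughly 15% to 47% of trials.

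These figures rest on an assumed trend size, equal enrolment per unit-period, end-of-stay incidence rather than the full curve, and about 7,200 patients. That last number is uncertain, because patients with an interpreter before identification are excluded. The article gives both 35 units and 12 clusters; that inconsistency is a separate matter, and the conclusion is the same under either. The primary outcome analysis and the main proportional-odds analysis are sound on this point.

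**What to change.** Add a sentence stating that pooled cumulative incidence curves by arm are descriptive only and carry no p-value or treatment-effect interval.

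If an effect is to be estimated under the competing-risk approach, specify a model, for example Fine-Gray or cause-specific hazard, with death or discharge as the competing event, terms for intervention and time period, and unit clustering handled by robust variance or a frailty. The functionally similar wording can stay.

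The cost is a sentence or two and slightly more programming; no new data are needed. The adjusted interval will be wider than the pooled one, because the all-control first period and all-intervention last period add little to a within-period contrast.
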